## Abstract

**Background**: Current guidelines acknowledge that early discharge is not associated with late mortality and that in-hospital length of stay (LOS) of 48–72 h should be considered following successful primary percutaneous coronary intervention (PPCI) in low-risk patients. Recent studies have highlighted the safety of very early discharge after PPCI in highly selected low-risk patients; however, objective tools to guide discharge timing remain limited. The Index of Microcirculatory Resistance (IMR) offers a quantitative assessment of microvascular function and may help identify patients suitable for very early discharge. We aimed to evaluate the feasibility of using IMR to guide very early discharge in patients who underwent uncomplicated PPCI. **Study design and objectives**: The Safety of Early Discharge Using Index Microcirculatory Resistance in Patients with Acute Myocardial Infarction (SECURE) study is designed to assess the feasibility of using IMR, measured immediately following successful PPCI, to guide early discharge from hospital within 24 h. The SECURE study is a prospective, proof-of-concept, functional non-inferiority, single-centre, randomised, open-label trial to determine if patients with low IMR can be safely discharged when compared to standard discharge policy. The SECURE study will recruit 82 patients with low IMR following successful PPCI. Participants will be 1:1 randomised to either standard discharge timing or very early discharge (within 24 h). The left ventricle ejection fraction will be assessed using cardiac magnetic resonance imaging. A telephone follow-up at 3 months will be arranged. Clinical events are collected as secondary and exploratory safety endpoints. **Conclusions**: The SECURE study will provide proof-of-concept data about the feasibility of using IMR to guide very early discharge following PPCI. If successful, this study will provide data to plan for a larger study to determine the safety of this personalised approach.

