#### 3.4.3. Randomisation

The SECURE study will only randomise participants who have preserved microvascular function as defined by IMR ≤ 40. Based on previous studies [7,14], we expect that two-thirds of patients with good procedural outcomes, including TIMI 3 flow, will have preserved microvascular function as defined by the SECURE study methodology.

Once microvascular function assessment is performed, patients with IMR ≤ 40 will be 1:1 randomised by means of a web-based randomisation secure method with no stratification block. Blinding or masking of the randomisation group cannot be applied, given the nature of the study. Therefore, patients as well as physicians will be aware of the discharge strategy; however, the analysis of the primary endpoint of left ventricular function will be blindly performed.

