### 3.6. Statistical Analysis

The obtained data will be assessed for normality distribution and reported as means (and standard deviation) or medians (and inter-quartile range) accordingly. The primary endpoint of left ventricle ejection fraction will be compared according to the in-hospital LOS groups using an unpaired *t-test* (or Mann–Whitney U test if appropriate). Other cardiac MRI endpoints, such as left ventricle volume and infarct size, will be evaluated using standard statistical tests depending on whether the data will be normally distributed or skewed. The composite clinical endpoints will be assessed with the use of cumulative incidence curves and the estimated Cox proportional hazards model. Each component of the clinical endpoints will be similarly compared between the two groups using chi-square or Fisher’s exact test, as appropriate.

The study is designed to establish the non-inferiority of early discharge compared to standard practice on left ventricle function at three months following STEMI presentation in patients with preserved microvascular function. Previous data suggested that left ventricle ejection fraction was 46 ± 8% in patients presenting with STEMI who underwent an uncomplicated procedure with final TIMI 3 flow and were hemodynamically stable post PPCI [16,17]. Assuming a non-inferiority margin of 5% difference in left ventricle ejection fraction with 80% power at an alpha level of 0.025, a sample size of 82 patients is required (41 patients in each group). An absolute difference of 5% in LVEF was selected based on prior studies, whereas differences in this magnitude are generally considered within the range of measurement variability and unlikely to translate into meaningful differences in clinical outcomes, particularly in haemodynamically stable, low-risk patients [16,18]. Given that 25% of patients presenting with STEMI and TIMI 3 flow will have IMR > 40 [19], and assuming that 5% of included patients will be lost to follow-up, the total sample size is estimated as 122 patients. The primary analysis will be conducted according to the intention-to-treat principle, but per-protocol analysis will also be performed. Missing CMR data will be handled using predefined sensitivity analyses.

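### The total of 122 does not follow from its stated inputs (which give 116 to 118), two different IMR yields are assumed, and the abstract's 82 allows for no loss

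*Protocol article*

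**What the plan says.** Section 3.6 of the protocol article sizes the trial on 3-month LVEF by CMR. It takes from earlier data that "left ventricle ejection fraction was 46 ± 8" percent, and sets out its design assumptions: "Assuming a non-inferiority margin of 5% difference in left ventricle ejection fraction with 80% power at an alpha level of 0.025". From these it derives a requirement of 82, split as 41 per arm. It then makes two adjustments. The first is that "25% of patients presenting with STEMI and TIMI 3 flow will have IMR > 40". The second is the loss allowance, with the result: "assuming that 5% of included patients will be lost to follow-up, the total sample size is estimated as 122 patients".

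Two other places bear on the same numbers. Section 3.4.3, which restricts randomisation to low-IMR patients ("patients with IMR ≤ 40 will be 1:1 randomised"), states that "we expect that two-thirds of patients with good procedural outcomes, including TIMI 3 flow, will have preserved microvascular function". The abstract states: "The SECURE study will recruit 82 patients with low IMR following successful PPCI".

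Section 3.1 allows recruitment to be extended if the target sample size is not met by the planned end date. It does not say which number is that target. It also describes a parallel registry of patients with IMR above 40.

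**The concern.** Section 3.6 prints both the inputs and the result, so a reader can check one against the other, and they disagree. The share of patients with IMR above 40 is 25% in Section 3.6 and, by implication, about one third in Section 3.4.3. Both are planning figures for what is essentially the same group, patients with TIMI 3 flow after PPCI. The abstract's recruitment figure is the same 82 that Section 3.6 derives before any loss.

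At stake are how many patients must be randomised to keep the stated power, how many must have IMR measured to find them, and which number the extension provision in Section 3.1 refers to.

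**Working it through.** **Inputs.** From Section 3.6: SD 8, margin 5 points, power 80%, alpha 0.025, IMR above 40 in 25%, loss 5%, stated total 122. From Section 3.4.3: IMR of 40 or below in two-thirds. From the abstract: 82 low-IMR patients. The true difference is taken as zero and alpha as one-sided; the article states neither, but with these the plan's 82 reproduces.

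**Step 1, the base figure.** n per arm = 2 × SD² × (1.960 + 0.842)² / margin² = 2 × 64 × 7.851 / 25 = 40.2, so 41 per arm and 82 in total. This matches Section 3.6. Power at 41 per arm is 80.8% by the normal approximation and 79.8% by the noncentral t.

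**Step 2, the total from the stated inputs.**
- Direct: 82 / 0.95 / 0.75 = 115.1, so 116.
- Rounding at each step: 82 / 0.95 = 86.3, so 87; 87 / 0.75 = 116.
- Equal arms: 41 / 0.95 = 43.2, so 44 per arm and 88 randomised; 88 / 0.75 = 117.3, so 118.
- Adding the two percentages: 82 / (1 − 0.25 − 0.05) = 117.1.
- Loss as a mark-up: 82 × 1.05 / 0.75 = 114.8.
- Both as mark-ups: 82 × 1.25 × 1.05 = 107.6.

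None of these gives 122.

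**Step 3, the total under the Section 3.4.3 yield.** 82 / 0.95 / (2/3) = 129.5, so 130. Rounding at each step gives 87 / (2/3) = 130.5, so 131. Equal arms give 88 / (2/3) = 132.

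The stated 122 lies between the two assumptions. With 5% loss it would be exact if the share with IMR above 40 were 1 − 82 / (0.95 × 122) = 29%, a rate that appears nowhere in the article.

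**Step 4, what each reading delivers.** Normal power = Φ(5 / (8 × √(2/n)) − 1.960), with n evaluable per arm. The t figures use the noncentral t with 2n − 2 degrees of freedom.

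| Reading | Randomised | Evaluable after 5% loss | Power, t | Power, normal |
|---|---|---|---|---|
| 82 evaluable (the requirement) | – | 82 | 79.8% | 80.8% |
| 122 assessed, 25% above 40 | 122 × 0.75 = 91.5 | 86.9 | about 82% | about 83% |
| 122 assessed, one third above 40 | 122 × 2/3 = 81.3 | 77.3 | about 77% | about 78% |
| 82 randomised (abstract) | 82 | 77.9 | 77.8% | 78.8% |

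**The case against.** The strongest reply is that the discrepancy is harmless. At Section 3.6's own 25% rate, 122 is more than needed and gives power above the target. The base of 82 is right. Even in the unfavourable readings the loss is two to three points on either basis, in a single-centre proof-of-concept trial. All of this stands, and it sets the severity.

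It is also fair to say that 82 and 122 count different stages: low-IMR patients, and the total before the IMR exclusion and loss. Their difference is not a contradiction. A reader might infer that the plan carries three incompatible targets, with 87 as the third. The article does not support that, because 87 or 88 is derived here and printed nowhere in it. A reader might likewise infer that the whole plan ignores loss. It does not: Section 3.6 applies the 5% in reaching 122, and only the abstract's 82 leaves it out.

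The two yields are rounded and come from different cited sources. The yield governs how many patients must be assessed, not how many must be randomised. That limits the consequence of the conflict but does not remove it, since the 122 is built on one of the two rates.

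Reading 122 as randomised patients plus the high-IMR registry does not rescue it, because that sum is again the number assessed.

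It is tempting to explain where 122 came from. Applying the 5% twice gives 87 / (0.95 × 0.75) = 122.1, and the two-thirds yield with no loss gives 82 / (2/3) = 123. The article supports neither account, and the point does not depend on either.

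**Conclusion.** The point holds as a modest one. The total of 122 does not follow from 82, 5% and 25%, which give 116, or 118 with equal arms. Sections 3.4.3 and 3.6 use different IMR yields, and 122 matches neither: it is 4 to 6 above the need at 25% and 8 to 10 below it at one third. The abstract's 82 is the requirement before the stated loss.

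A reader might conclude that the trial is underpowered. The article does not support that. At the rate Section 3.6 uses, 122 is conservative. In the other readings power falls to about 77% to 79%, against 79.8% (t) or 80.8% (normal) with the full 82. Nor does any section say that recruitment stops at 82 randomised regardless of loss, or at 122 assessed; those are scenarios, and Section 3.1 allows an extension.

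These figures assume SD 8, a true difference of zero, a one-sided alpha of 0.025 and loss of exactly 5%. Validity is not threatened. What needs correcting is a sample-size statement that cannot be reproduced from its own inputs.

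**What to change.** Choose one rate for IMR above 40 and use it in both Section 3.4.3 and Section 3.6. Then state three numbers separately:
- 82 with an evaluable 3-month CMR (41 per arm);
- 88 randomised (44 per arm), which covers the 5% loss;
- the matching number with IMR assessed: 118 at 25%, or 132 at one third.

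Say in Section 3.1 that the recruitment target is the number randomised, so that the extension provision has a definite meaning. Correct the abstract to match, making clear whether its figure is before or after loss. If 82 randomised is what is intended, keep it and restate the power as about 78% to 79%.

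The cost is a few restated figures. Design, endpoint and margin do not change. At the 25% rate the 88 randomised fit within the 122 already planned (122 × 0.75 = 91.5). At one third, about 10 more patients would need IMR assessment (132 − 122).

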### 3.7. Ethics and Regulatory Considerations

The investigators will ensure that the SECURE study will be conducted in accordance with relevant regulations, Good Clinical Practice, and the principles of the Declaration of Helsinki. The protocol and all patient-facing documents have been submitted and received approval from the South East Scotland Research Ethics Committee 01 (reference number 23/SS/0116). The investigators will submit and, where necessary, obtain approval for all substantial amendments to the original approved documents.

Direct access will be granted to authorised representatives from the Sponsor or host institution for monitoring and/or audit of the study to ensure compliance with regulations. Any audit or monitoring visit will be done in accordance with the current approved protocol, GCP, relevant regulations and standard operating procedures.

## 4. Discussion

The SECURE study will be the first study to apply the use of coronary microcirculation assessment to identify STEMI patients who may be candidates for early hospital discharge, i.e., within 24 h. This study will aim to address a major gap in contemporary PPCI care related to the absence of an objective approach to guide decisions regarding in-hospital LOS. Current guidelines acknowledge that short in-hospital LOS of less than 72 h is not associated with adverse events in low-risk patients following successful PPCI [3].

Several risk models were proposed to identify candidates for early discharge, including the Second Primary Angioplasty in Myocardial Infarction (PAMI-II) criteria, and the Zwolle primary PCI Index [1,20,21]. However, those risk models were derived using data from more than two decades ago, and contemporary PPCI has significantly evolved with better triage to minimise delay to the catheterisation laboratory, as well as improvement in pharmacological and non-pharmacological treatments, including stent designs. More recent studies reported the safety of very early discharge of less than 48 h in patients presenting with STEMI and undergoing successful PPCI [17,22]. Nonetheless, these studies relied on certain clinical and angiographic markers, such as infarct location, presence of multi-vessel disease, and multi-vessel PCI, to aid decision-making regarding early discharge [17,22]. Despite being considered low risk, a significant proportion of patients stayed in-hospital for more than 48 h, highlighting a potential selection bias and the need to use a more reliable metric to identify patients who are candidates for early hospital discharge [17,22]. Moreover, such a metric needs to reflect the pathophysiological process and can characterise the injured myocardium (and microvascular function) to safely guide early hospital discharge.

IMR provides a robust measure of microvascular integrity and has shown excellent ability in predicting the recovery of left ventricle function [5]. It has also been linked to clinical outcomes, and major clinical adverse events were significantly higher in patients with IMR > 40 compared to those with IMR ≤ 40 (17.1% vs. 6.6%, *p* = 0.027) [10]. In fact, IMR > 40 was associated with more than a 4-fold increase in risk of death and heart failure at one year [7,23]. Importantly, IMR exists as a continuum, and a pooled analysis of 1265 patients from 6 cohorts highlighted that serious adverse clinical events such as cardiac death can be predicted using a higher IMR cutoff (above 70) in patients presenting with STEMI [24]. Nonetheless, the same study highlighted that IMR above 40 was associated with more cardiac death, a higher composite of cardiac death and heart failure, a larger infarct size and more frequent microvascular obstruction and intra-myocardial haemorrhage [24]. Whilst dichotomisation may reduce granularity, the selected binary threshold was chosen to enhance clinical interpretability and real-world applicability of the discharge strategy.

The randomisation process within the SECURE study is planned without any stratification. An imbalance between treatment groups may be prevented using stratification for known factors that influence prognosis [25]. There are several clinical and angiographic features that are considered key prognostic variables in patients presenting with STEMI; however, their interaction with the short length of stay is yet to be determined. Overall, IMR may serve as a useful tool to identify patients who may be at low risk of early adverse events and potentially suitable for early discharge from the hospital.

In a previous study that included 261 patients who underwent PPCI, the incidence of cardiac complications before hospital discharge or within 30 days, defined as the composite of cardiac death, cardiogenic shock, pulmonary oedema, malignant arrhythmias, cardiac rupture, and presence of left ventricular thrombus, was 8.4% (22 out of 261). IMR ≤ 40 was recorded in all patients without in-hospital complications [7]. On the other hand, 1 in 7 patients with IMR > 40 was associated with in-hospital adverse events [7]. It had a sensitivity of 100% with a negative predictive value of 100% and outperformed existing criteria for early discharge, such as PAM-II and the Zwolle scores [7].

By incorporating IMR into discharge decision-making, clinicians may be able to identify patients at low risk of complications while reducing unnecessary hospitalisation.

If early discharge guided by IMR proves non-inferior in terms of LV functional recovery—and safe, acceptable to patients, and cost-effective—the SECURE strategy could transform post-STEMI pathways, reduce bed occupancy, and optimise resource allocation across healthcare systems. Importantly, the SECURE study targets selected low-risk patients presenting with STEMI who underwent a successful procedure without hemodynamic instability. The enrolment of this narrow STEMI subgroup would not enable physicians to apply the study’s findings to a broader population and would limit its generalisability. Implementing an IMR-guided early discharge strategy requires a larger study to ensure the safety of this approach.

In conclusion, the SECURE study will provide proof-of-concept data about the feasibility of using IMR to guide very early discharge following PPCI. If successful, this study will provide data to plan for a larger study to determine the safety of this personalised approach.

## Figures and Tables

**Figure 1 jpm-16-00207-f001:**
[figure not shown]
Study flow chart.

**Figure 2 jpm-16-00207-f002:**
[figure not shown]
An illustrative example of coronary microcirculation assessment using PressureWire™ X. The top row represents a patient with preserved microcirculation function (IMR less than 40), and the bottom row illustrates a patient with impaired microcirculation assessment (IMR above 40). Blue curves show resting transit times and orange shows hyperaemic transit times. Resting as well as hyperaemic pressure and flow indices are displayed on the right side of the Figure.

**Table 1 jpm-16-00207-t001:** Inclusion and exclusion criteria of the SECURE study.

Inclusion criteria
Age 18–90 years
Successful revascularisation with TIMI 3 flow
Haemodynamic stability following PPCI Preserved microvascular function, defined as IMR ≤ 40
Ability to provide verbal consent
Exclusion criteria
Out-of-hospital cardiac arrest
Suboptimal angiographic results
Previous coronary artery bypass grafting
Cardiogenic shock or pulmonary oedema
Planned staged PCI during index admission
Known contraindication to adenosine
Known contraindication for CMR
Pregnancy or breastfeeding

**Table 2 jpm-16-00207-t002:** Primary and secondary objectives of the SECURE study.

Objectives	Outcome Measures	Evaluation Timepoints
Primary Objective Impact of early discharge on left ventricle function in STEMI patients with preserved microvascular function	Left ventricle ejection fraction as estimated on CMR	3 months
Secondary Objectives (a) Safety of early discharge strategy	The composite of all-cause mortality, recurrent myocardial infarction, unplanned revascularisation, readmission with heart failure, cardiac arrest, sustained ventricular tachycardia/fibrillation, and cardioverter defibrillator implantation.	3 and 12 months.
(b) Cost-effectiveness	The potential cost-saving of using coronary physiology to guide early hospital discharge in patients presenting with STEMI and preserved microvascular function.	3 months
(c) Impact on functional status	The severity of angina symptoms and functional status in STEMI patients with preserved microvascular function according to their hospital discharge policy	3 months

## Data Availability

The raw data supporting the conclusions of this article will be made available by the authors on request.
